#### Data collection, management and storage

Data collection tools include survey instruments and results of the outcome tests described above. All participant data will be collected using ID codes to maintain confidentiality and enable the participant’s tracking throughout the study period. All laboratory specimens will also be labelled with sample ID codes.

#### Statistical analysis

To assess the effect of amino acid supplementation on markers of gut function in stunted children, we will first calculate summary values for the LR, ^13^C-SBT and the DSIT. Each of these tests may be summarised in various ways, and so our primary and secondary summary measures for each test are determined a priori. The LR test is the urinary excretion ratio (% of lactulose dose excreted/% of rhamnose dose excreted) over the test period; % lactulose excretion and % rhamnose excretion will be included as secondary outcomes. For the ^13^C-SBT, increases in atom per cent excess over baseline abundance will be converted to percentage of dose recovered (PDR) and curves are fit to the series of breath samples from each participant breath. From these breath curves, the time at which 50% of the final test dose is recovered (T_50_) will be considered as a primary outcome of interest. This choice is based on prior work that demonstrates that T_peak_ and T_50_ are associated with intestinal sucrase activity compared with other aspects of sucrose metabolism (eg, the fraction of the plasma bicarbonate excreted on the breath as opposed to excreted in urine or sequestered).^36^ Other summary measures of the ^13^C-SBT such as cumulative PDR by 90 min may also be influenced by misspecifications of CO_2_ production rate (VCO_2_), which is based on the participant’s estimated body surface area and sex.^52^ The DSIT is summarised as the % digestibility of specific amino acids from spirulina. The method of estimation is summarised in Devi *et al*.^21^ Weight-for-age Z-scores will be calculated based on WHO reference standards.^53^ Plasma concentrations LPSBP and iFABP and faecal concentrations of MPO and NEO will also be analysed.

For all statistical analysis, p values <0.05 will be considered statistically significant and intention-to-treat analyses will be applied. Both our primary and secondary outcomes will be analysed as change from baseline to endline. Because LR ratios are generally not normally distributed, we will use the non-parametric Wilcoxon rank-sum test to compare the supplementation and control groups within each site. For combined analyses we will use logistic regression models (outcome: LR ratio above vs below EE cut-off, exposure: intervention or control group). For all secondary outcomes, we will similarly use the non-parametric Wilcoxon rank-sum test to compare the supplementation and control groups within each site. For combined analyses we will use linear regression models or logistic regression models based on appropriate cut-off values, including a random effect to account for clustering by site.

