#### Outcomes and case definitions

We will collect child stool, blood, urine and breath samples, both at baseline and endline, to conduct the following tests of intestinal status and function. All outcome measures for this study are expressed as changes from baseline.

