### Sample size

The sample size for this study is based on the minimum number of participants necessary to observe differences in the primary outcome variable (ΔLR) between intervention and control groups.^47 48^ Each site will contribute data from 60 children, for a total of 360 children across six sites. Assuming an intraclass correlation coefficient (ICC) of 0.1 in ΔLR ratios based on prior reports,^49^ this is sufficient to detect a standardised effect size of 0.40 or greater (a change in ΔLR equal to or greater than 0.4 SD) with an α value of 5% and 80% power. This is equivalent to changes in LR reported in response to other nutritional interventions^47 48^ and is substantially greater than previously reported effect sizes for glutamine and glycine.^50^ A sample size of 60 participants is also sufficient to detect within-site differences with a standardised effect size of 0.84 or greater (ΔLR equal to or greater than 0.84 SD). This difference is on the order of the prior reports of glutamine and glycine supplementation.^50^ Assuming a similar ICC for DSIT results, the same effect sizes (0.40 or greater for pooled analyses and 0.84 or greater for within-site analyses) would be detectable. A prior study on specific amino acid absorption in children within and without EE reported differences in mean amino acid absorption between the group equivalent to an effect size of 0.5.^51^ However, our study will be the first to use the DSIT to evaluate changes in protein digestion associated with a nutritional intervention.

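### Within each site every outcome is tested as an unadjusted change from baseline by a rank test; this is valid but gives up precision that baseline adjustment would recover at no cost in data

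*Protocol article*

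**What the plan says.** Under Outcomes and case definitions the article states that "All outcome measures for this study are expressed as changes from baseline", and also that "We will collect child stool, blood, urine and breath samples, both at baseline and endline". Statistical analysis repeats the choice: "Both our primary and secondary outcomes will be analysed as change from baseline to endline". For the primary outcome it gives the reason for a rank method ("Because LR ratios are generally not normally distributed") and then the method: "we will use the non-parametric Wilcoxon rank-sum test to compare the supplementation and control groups within each site". All secondary outcomes are handled the same way within site.

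The combined analyses differ. For LR: "For combined analyses we will use logistic regression models (outcome: LR ratio above vs below EE cut-off, exposure: intervention or control group". For secondary outcomes: "For combined analyses we will use linear regression models or logistic regression models based on appropriate cut-off values, including a random effect" for site. Sample size sets the scale: "Each site will contribute data from 60 children, for a total of 360 children across six sites", half in each arm, so 30 against 30 within a site. It gives a within-site detectable difference of 0.84 SD of the change in LR.

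**The concern.** Subtracting baseline fixes its coefficient at 1. That is the best choice only when baseline and endline are almost perfectly correlated. At lower correlations the difference carries the measurement noise of both visits, and regressing endline on baseline removes more variation. A rank-sum test on the differences cannot recover this because it has no place for a covariate.

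There is a second loss for LR, myeloperoxidase (MPO), neopterin (NEO), iFABP and LPSBP. If such a measure is skewed, children with high values produce the largest raw differences in either direction. Ranking limits the influence of extremes, but the ordering is still set on the raw scale.

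What is at stake is power within sites of 60 children, where by the article's own figure only a large effect is detectable.

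**Working it through.** **Inputs from the article.** 30 per arm per site; change from baseline; Wilcoxon rank-sum within site; alpha 5% (two-sided assumed), 80% power; stated within-site detectable effect 0.84 SD of change.

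**Assumed, because the article does not give them.** The baseline-endline correlation r; equal variances at both visits; for the power figures, lognormal data with log-SD 0.8 and a multiplicative effect of 0.7 SD on the log scale.

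**The plan's own figure.** Detectable difference = (1.960 + 0.842) × √(2/30) = 0.72 SD, not 0.84. At 0.84 SD the power is Φ(0.84 × √15 − 1.96) = 90%. So 0.84 matches 90% power, or 80% power with about 24 evaluable children per arm. That mismatch is a separate matter and does not affect what follows.

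**Variance on a common scale.** With outcome variance s² at each visit:
- change score: 2(1 − r)s²
- baseline-adjusted: (1 − r²)s²
- ratio: (1 − r²) / [2(1 − r)] = (1 + r)/2

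| r | Ratio | Stated 0.84 SD becomes (× √ratio) |
|---|---|---|
| 0.2 | 0.60 | 0.65 |
| 0.5 | 0.75 | 0.73 |
| 0.8 | 0.90 | 0.80 |

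The last column takes 0.84 at face value and stays in SDs of the change score.

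**Closed-form power on the log scale** (30 per arm, effect 0.7 SD, normal approximation):
- r = 0.3, change: SD √1.4 = 1.183; 0.7/1.183 = 0.592; × √15 = 2.29; power Φ(2.29 − 1.96) = 63%.
- r = 0.3, adjusted: SD √0.91 = 0.954; 0.734; 2.84; power 81%.
- r = 0.5, change: SD 1.000; 0.700; 2.71; power 77%.
- r = 0.5, adjusted: SD √0.75 = 0.866; 0.808; 3.13; power 88%.

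**Simulated power, same setting** (at least 2,000 trials per cell, so the Monte Carlo error is about 1 point):

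| Method | r = 0.3 | r = 0.5 | r = 0.8 |
|---|---|---|---|
| Wilcoxon, raw change (as planned) | 44% | 57% | 90% |
| Wilcoxon, log change | 59% | 72% | 98% |
| ANCOVA, log scale | 79% | 86% | 99% |

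The simulated values for the last two methods sit a few points or less below the closed form where both are given, as expected for a rank test and a t reference with 60 children. Type I error was about 4–6% for every method.

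**Splitting the gain.** At r = 0.3 the log scale gives 59 − 44 = 15 points and baseline adjustment 79 − 59 = 20. At r = 0.5 the split is 72 − 57 = 15 and 86 − 72 = 14. At r = 0.8 adjustment alone adds about 1 point.

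**Sensitivity to skewness.** With log-SD 0.5, raw-change Wilcoxon has 49% and 63% power at r = 0.3 and 0.5; with log-SD 0.3 it has about 53% and 68%. The scale gain therefore shrinks as the data become less skewed.

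**The case against.** The strongest defence is that the plan is prespecified and valid. Under randomisation the change-score comparison is unbiased, and the rank test holds its type I error. That stands. A reader might infer that chance baseline imbalance biases the result through regression to the mean. It does so only conditionally on the imbalance that happens to arise; over repeated randomisation it is part of the sampling error.

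A reader might also infer that every outcome in the trial is analysed as an unadjusted change score. The article does not support that. The combined LR analysis is a logistic model of LR above or below a cut-off, which is not a change score. The combined secondary models neither name nor exclude a baseline covariate, and an analysis plan not shown here may settle it.

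Nor does log-scale ANCOVA give the same answer on a different scale. The null hypothesis agrees, but the estimand becomes a ratio of geometric means instead of a difference in raw change. For example, a 20% reduction is ln 0.8 = −0.223 at any LR level. Under assumed lognormal data with r = 0.4, the difference in mean raw change runs from −0.023 to −0.110 as the median LR goes from 0.1 to 0.4 and the log-SD from 0.5 to 0.8.

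The size of the gain is also open to challenge. It depends on an r that the article does not give, and the lognormal, multiplicative model favours the log scale. This stands too, and is why the gains are shown as a range and split by source.

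Finally, baseline is not available for every test in every child: Table 2 shows that Zambia does neither the dual stable isotope test (DSIT) nor the ¹³C sucrose breath test.

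An unseen analysis plan does not answer the remaining point. For the within-site comparisons the article itself fixes both the change score and a test that cannot take a covariate.

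**Conclusion.** The point holds for the within-site comparisons of the primary and all secondary outcomes. It is a loss of efficiency, not a bias or an error of validity. On a common scale with equal variances, adjustment cuts variance by 40% at r = 0.2, 25% at r = 0.5 and 10% at r = 0.8. For LR under the assumed lognormal model, moving from the planned test to log-scale ANCOVA raises within-site power from about 44% to 79% (r = 0.3) or from 57% to 86% (r = 0.5), with roughly half of that due to scale and half to adjustment. At r of 0.8 or above there is little to gain from adjustment alone. The conclusion does not extend to the pooled primary logistic model.

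**What to change.** For the within-site comparisons, make the main analysis the endline value adjusted for the baseline value: on the log scale for LR, MPO, NEO, iFABP and LPSBP, and untransformed for DSIT digestibility, breath-test T50 and weight-for-age z (which can be negative and cannot be logged). Report the adjusted difference or ratio with a 95% CI, and keep the Wilcoxon test on change as a sensitivity analysis. Where a pooled linear model of a secondary outcome is used, include baseline as a covariate alongside the site effect.

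State that for logged outcomes the effect is a ratio of geometric means. The sentences that express every outcome as a change, and the sample-size statement in SDs of the change in LR, should be aligned with this. The cost is that rewording, agreed before any comparison by arm; no extra children, visits or samples are needed.

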**Methods and analysis:**

We will conduct coordinated randomised controlled trials in six countries to determine if supplementation with indispensable amino acids (IAAs) can improve intestinal barrier dysfunction in six geographically diverse populations of 18–36 months old children with stunting or severe stunting. All trials will measure the same primary outcomes while secondary outcomes will be measured on a per-trial basis using standardised protocols across the project. The primary endpoint will be change in gut permeability as assessed by the lactulose/rhamnose ratio. Secondary endpoints include changes in amino acid and carbohydrate absorption using novel, isotope tracer tests. Other prespecified outcome measures include changes in EE biomarkers and child weight. IAA supplementation will be given daily for 28 days and evaluation of the major endpoints will be at baseline and after 28 days of supplementation.

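### The pooled primary analysis models whether LR is above or below a cut-off, but the declared and powered endpoint is change in LR

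*Protocol article*

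**What the plan says.** Four places in the protocol article put the primary outcome on the scale of change:

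- Abstract, Methods and analysis: "The primary endpoint will be change in gut permeability as assessed by the lactulose/rhamnose ratio".
- Outcomes and case definitions: "All outcome measures for this study are expressed as changes from baseline".
- Sample size: the number of children is the minimum "necessary to observe differences in the primary outcome variable (ΔLR) between intervention and control groups". The pooled sample of 360 is said to detect 0.40 SD of ΔLR with 80% power at α 5%, and 60 children within a site to detect 0.84 SD.
- Statistical analysis: "Both our primary and secondary outcomes will be analysed as change from baseline to endline".

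The Statistical analysis section then gives non-normality of LR as the reason that, at site level, "we will use the non-parametric Wilcoxon rank-sum test to compare the supplementation and control groups within each site". For the six sites together it says: "For combined analyses we will use logistic regression models (outcome: LR ratio above vs below EE cut-off", with study arm as the only listed exposure. This is the only combined analysis of LR that the article names. For secondary outcomes the combined model may be linear or logistic, so the restriction to a binary form falls on LR alone. No power is stated for a binary outcome.

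**The concern.** The pooled comparison is the only one sized for a moderate effect, and the ethics and dissemination section says the primary outcomes will be published together. It is therefore the analysis on which the trial will be judged, and as written it answers a question other than the declared one.

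Three things follow.

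- The sample-size statement does not describe the model that will be fitted.
- A site analysis and the pooled analysis can disagree simply because one compares ranks of change and the other compares odds of exceeding a threshold.
- A change in LR that does not carry a child across the threshold adds nothing to the pooled result, although it counts fully in the declared endpoint. Children are enrolled on stunting (Table 4), with no LR criterion, so some may start well away from the threshold.

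Skewness explains the rank test. It does not require dichotomising, because a log transform or a site-stratified rank test handles it and keeps the ordering of the values.

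**Working it through.** **1. The mismatch.** This needs no arithmetic. The endpoint, the general outcome statement, the sample size and the opening of the analysis paragraph all concern change. The combined LR model concerns position relative to a threshold. Both cannot describe the primary analysis.

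**2. The plan's own figure.** Inputs from the document: 360 children, 1:1 (180 per arm), α 5% (two-sided assumed), effect 0.40 SD of ΔLR.

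- Power for continuous ΔLR: Φ(0.40·√(180/2) − 1.96) = Φ(3.795 − 1.96) = 96.7%.
- Effect detectable with 80% power: (1.96 + 0.842)·√(2/180) = 0.295 SD.

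The stated 0.40 SD at 80% does not reproduce from the plain formula. It would need about 98 effective children per arm (a design effect of about 1.83). That is a separate point. Here it means that the binary analysis should be compared with both 97% and the claimed 80%.

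**3. The binary outcome.** Assumptions not in the document: normal shift; equal SDs at baseline and endline; correlation r between them; the outcome is endline status; p0 is the control proportion above the cut-off at endline.

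- Effect in endline SDs: d = 0.40·√(2(1 − r)), which is 0.506 at r=0.2, 0.400 at r=0.5 and 0.310 at r=0.7.
- Intervention proportion above the cut-off: p1 = Φ(Φ⁻¹(p0) − d).
- Power = Φ{[(p0 − p1) − 1.96·√(2p̄(1 − p̄)/180)] / √([p0(1 − p0) + p1(1 − p1)]/180)}, where p̄ is the mean of p0 and p1.

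Example, r=0.5 and p0=0.50: p1 = Φ(−0.40) = 0.345, and p̄ = 0.422. The null standard error is 0.0521 and the alternative one 0.0514. Power = Φ((0.1554 − 0.1020)/0.0514) = Φ(1.04) = 85%.

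Power (%) at 0.40 SD of change, 180 per arm:

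| Controls above cut-off | r=0.2 | r=0.5 | r=0.7 |
|---|---|---|---|
| 10% | 66.0 | 49.8 | 34.6 |
| 20% | 85.3 | 68.7 | 49.0 |
| 30% | 92.4 | 78.0 | 57.3 |
| 50% | 96.6 | 85.0 | 64.4 |
| 70% | 96.5 | 84.2 | 62.5 |
| 80% | 94.7 | 79.7 | 57.1 |
| 90% | 87.3 | 67.2 | 45.0 |
| Continuous ΔLR | 96.7 | 96.7 | 96.7 |

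If the stated 80% is instead taken as given (98 effective per arm), binary power for 20–90% above the cut-off is 60–79% at r=0.2, 43–60% at r=0.5 and 27–40% at r=0.7.

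**4. Separating dichotomising from other choices.** This simulation used log-normal LR, six sites of 60, within-site SD of log LR 0.8, between-site SD 0.4, a true effect of 0.30 SD of log LR, r from 0.2 to 0.5, and the cut-off at the 20th, 50th or 80th percentile. All of these except the site numbers are assumed. Approximate power:

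- logistic on arm only: 38–55%
- linear, raw ΔLR, with site: 36–53%
- linear, change in log LR, with site: 60–82%
- endline log LR on arm, baseline log LR and site (ANCOVA): 81–91%

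With skewed data, then, raw ΔLR does about as badly as the logistic model. Most of the advantage of the last model comes from the log scale and baseline adjustment.

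**The case against.** The strongest reply concerns power. A reader might infer that the logistic analysis forfeits much of the power claimed. The document does not support that. The claim is 80% at 0.40 SD; by the plain formula the binary analysis reaches about that or more at r=0.5 when 50–80% of controls are above the cut-off, and 85% or more at r=0.2 across 20–90%. The large gap is against 97%, which the protocol never claims. Neither r nor the cut-off prevalence is given, and real LR is skewed, so the normal-shift figures are illustrative. This objection stands, and the loss is stated here only as conditional.

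A reader might also take the gap between the logistic model and log-LR ANCOVA as the price of dichotomising. It is not, because raw ΔLR, the declared scale, performs much like the logistic model in the same simulation.

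Two further inferences go too far. One is that a child below the cut-off at baseline cannot contribute. Such a child can rise above it by endline, so prevented worsening counts in a randomised comparison. The other is that a real reduction would go undetected. Under a general shift some children do cross.

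Finally, the article lists arm as the exposure, but covariates and the cut-off value may be set out in an analysis plan that is not shown. Their absence is not held against the protocol. The binary outcome might also be built in some way from change, although the wording does not say so.

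None of this removes the contradiction between the named outcome of the combined model and the declared endpoint.

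**Conclusion.** The concern holds as a mismatch, with high confidence and at any correlation or cut-off. The combined LR analysis does not test change in LR, the 0.40 SD power statement does not cover it, and the site and pooled results estimate different quantities.

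Dichotomising usually costs power: on a normal scale it keeps at most 2/π = 64% of the information, at a median cut-off, and 34% with 90% above it. In this trial the cost could be nil (r=0.2, central cut-off) or large (r=0.7, or a cut-off far from the median). Confidence in a material loss is moderate at most until r and the prevalence are known. The reason to change the analysis is that it departs from the endpoint; the possible loss of power is secondary.

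**What to change.** Rewrite the combined-analysis sentence for LR:

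- **Primary:** a linear model of endline log(LR) on arm, baseline log(LR) and site, reported as a ratio of geometric means with 95% CI. State that this is how change in LR is assessed, and align the endpoint and sample-size wording with it.
- **Robustness check:** a site-stratified rank test of ΔLR, which matches the site-level analyses and the declared scale.
- **Secondary:** the cut-off logistic model, with the cut-off fixed in advance and adjustment for baseline status and site.

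The log-scale model is a preference among sound options, chosen for its handling of skewness and use of baseline. Any pooled continuous or rank analysis of change would remove the contradiction. The power statement should be restated for whichever model is chosen.

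The cost is one paragraph of analysis wording and a revised power sentence. Baseline and endline LR are already measured in every trial. Because the study is open label, the change should be made and dated before LR results are compared by arm.

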**Figure 2 F2:**
[figure not shown]
Coordinated research project design. A visual depiction of our coordinated research project design. AA, amino acid; 13C-SBT, 13C sucrose breath test; DSIT, dual stable isotope test; EE, environmental enteropathy; Gly-Sar, glycylsarcosine; iFABP, intestinal fatty acid binding protein; LPSBP, lipopolysaccharide binding protein; LR, lactulose/rhamnose test; MPO, faecal myeloperoxidase; NEO, faecal neopterin.

This is an open label study. In each trial, 18–36 months old children in the intervention arm will receive IAA supplementation for 28 days, while children in the control arm will receive only standard complementary foods for the same duration (figure 3). The study will be unblinded. Each of the six study sites will aim to recruit 60 children, half in the intervention arm and half in the control arm (see ‘Sample Size section’ for further details). Data collection began in August 2025 and is anticipated to be completed in all sites by June 2026. Site-specific start dates and enrolment status are reported in online supplement 1 (Standard Protocol Items: Recommendations for Interventional Trials (SPIRIT) guidelines for each site).

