#### Primary outcomes

*LR dual-sugar test*. The LR test is the most commonly used method to assess intestinal disruption in EE, because it is posited to measure intestinal permeability.^35^ At baseline and endline, the LR test will be administered. Guardians will be asked to fast their child for 1 hour prior to the appointment. A single urine sample will be collected before the start of the study and the time noted. At the start of the test, a 9 mL of drinking water spiked with 1 g lactulose and 0.2 g rhamnose will be administered, and again a 2 mL chaser of drinking water will be used to rinse the vial. The total volume (1 mL sucrose solution+2 mL chaser+9 mL LR solution+2 mL chaser) is 14 mL. All urine passed from 30 min up to 5 hours will be collected and pooled and the total volume noted. Water or breastmilk can be freely consumed throughout the test period. Sites have chosen between a possible 3-hour or a 5-hour LR collection protocols based on local logistical considerations (ie, ease of administration in young children).

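### The pooled primary logistic model for LR lists only treatment arm, although the six trials each allocate 30:30 and the pooled secondary models carry a site effect

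*Protocol article*

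**What the plan says.** All of this is in the protocol article.

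- **Pooled primary model (Statistical analysis).** "For combined analyses we will use logistic regression models (outcome: LR ratio above vs below EE cut-off", with "exposure: intervention or control group" as the only predictor named. No value is given for the cut-off.
- **Pooled secondary models (same paragraph).** After the text turns to the secondary outcomes, the combined linear or logistic models are described as "including a random effect to account for clustering by site".
- **Within-site analysis (same paragraph).** "we will use the non-parametric Wilcoxon rank-sum test to compare the supplementation and control groups within each site".
- **Design (Overview of the trial design, text after Figure 2).** "Each of the six study sites will aim to recruit 60 children, half in the intervention arm and half in the control arm". The section describes six coordinated randomised trials rather than one multisite trial.
- **Sample size.** 360 children in total, with an ICC of 0.1 assumed for the change in LR.
- **LR collection (Primary outcomes).** "All urine passed from 30 min up to 5 hours will be collected and pooled", and later in the same paragraph "Sites have chosen between a possible 3-hour or a 5-hour LR collection protocols based on local logistical considerations". Table 2 lists 3 hours for Morocco and Zambia and 5 hours for Ghana, India, Malawi and the Philippines.
- **LR summary (Statistical analysis).** The ratio of percentages of dose excreted is taken "over the test period". No conversion between windows is described.

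**The concern.** The plan specifies both pooled models and treats them differently: site is in the secondary models and absent from the primary one. Site is the unit within which children are allocated, and the plan itself expects sites to differ. It assumes a non-zero ICC and presents variety of setting as a strength. Table 3 shows food insecurity from 3% to 93.4%, and Table 4 mentions severe stunting for Zambia. The collection window also varies by site.

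In a logistic model, leaving out a factor that predicts the outcome moves the treatment odds ratio toward 1 even when that factor is balanced between arms, because the odds ratio is non-collapsible. At stake are some power for the primary pooled comparison, and a pooled odds ratio that does not estimate the same quantity as the within-site comparisons. A second issue is what being above the cut-off means when the ratio is accumulated over 3 hours in two sites and 5 hours in four.

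**Working it through.** **The plan's own figure.** No detectable odds ratio or power is given for the pooled logistic model. The nearest figure is 0.40 SD for the change in LR (N = 360, ICC 0.1, 5% alpha, taken as two-sided, 80% power). With 180 per arm and the ICC ignored, the detectable difference is (1.96 + 0.842) × √(2/180) = 0.295 SD.

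- Stratified by site, with within-site variance 0.9: 0.295 × √0.9 = 0.280 SD.
- Cluster design effect 1 + 59 × 0.1 = 6.9: 0.776 SD.
- Design effect 1 + 29 × 0.1 = 3.9: 0.583 SD.

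The stated 0.40 would need a design effect of (0.40/0.295)² ≈ 1.83, which none of these gives. That is a separate matter; only the assumed ICC is used below.

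**Inputs.** From the document: six sites, 30:30 in each, four 5-hour and two 3-hour sites, ICC 0.1. Assumed: within-site odds ratio 0.50, logit-scale ICC 0.1 to 0.5, and the share of controls above the cut-off.

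**Step 1: marginal against within-site odds ratio.** Let site intercepts on the logit scale be normal with variance s² = ρ/(1−ρ) × π²/3. For ρ = 0.1, s² = 0.111 × 3.290 = 0.366, so s = 0.60. The control share is the average of expit(a + s·x) over standard normal x, with a chosen to give the assumed overall share. The treated share adds ln 0.50 inside expit. The arm-only odds ratio follows from the two averaged shares.

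| ρ | s | control share 0.50 | 0.70 | 0.85 |
|---|---|---|---|---|
| 0.1 | 0.60 | 0.527 | 0.526 | 0.519 |
| 0.3 | 1.19 | 0.581 | 0.579 | 0.563 |
| 0.5 | 1.81 | 0.640 | 0.636 | 0.617 |

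At ρ = 0.1 the log odds ratio is 92.4% to 94.6% of the within-site value, a shrinkage of 5-8%.

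**Step 2: power and type I error by simulation.** Six sites of 60, 30:30, 1,500 runs per setting, with logistic models fitted with and without six site terms.

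| ρ | power, arm only | power, with site | type I error, arm only | type I error, with site |
|---|---|---|---|---|
| 0 | 91.1% | 91.1% | 4.7% | 5.1% |
| 0.1 | 87.6% | 88.7% | 3.9% | 4.6% |
| 0.3 | 75.1% | 81.5% | 3.0% | 4.5% |
| 0.5 | 58.7% | 73.1% | 1.9% | 5.0% |

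The gains are about 1, 6 and 14 points at ρ = 0.1, 0.3 and 0.5. One simulated power near 88% has a standard error of √(0.88 × 0.12/1500) = 0.8 points, so the first gain is small. The site-adjusted odds ratio averaged 0.49 against a true 0.50, a slight overshoot.

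**Step 3: a window difference alone.** Suppose 70% of controls exceed the cut-off in the four 5-hour sites and 30% in the two 3-hour sites.

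- Controls overall: (4 × 0.70 + 2 × 0.30)/6 = 0.567, odds 1.308.
- Treated shares at odds ratio 0.50: 0.538 and 0.176. Overall: (4 × 0.538 + 2 × 0.176)/6 = 0.418, odds 0.718.
- Arm-only odds ratio: 0.718/1.308 = 0.549. Wald power is 80% without stratification and 85% with it.

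With 70% in the 5-hour sites, a 3-hour share of 70% gives 0.50 (no change), 50% gives 0.514 (87% against 88%), and 20% gives 0.574 (74% against 82%).

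**The case against.** The strongest reply is that nothing is biased. With 30:30 in each site, arm and site are unrelated, so the arm-only odds ratio is a valid marginal odds ratio and its distance from the within-site value is a difference of estimand. This stands. A reader might infer confounding or an inflated false-positive rate. The balanced allocation rules out the first, and the simulation shows the reverse of the second.

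A reader might also infer that the odds ratio is certain to be materially attenuated. The documents do not support this. The between-site spread above the cut-off is not given, and at the plan's own ICC the loss is about one power point. In the other direction, that ICC is stated for the change in LR, whereas the pooled outcome is written as LR above or below a cut-off. Taking differences removes stable site differences, including a constant window effect, and a cut-off on the level keeps them. So 0.1 is not an upper bound.

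Nor do the documents establish that one cut-off serves both windows, or that 3-hour and 5-hour ratios are not comparable. The cut-off has no value, site details are placed in a supplement, and no data compare the windows.

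The random effect might have been meant for all combined analyses. Its place in the text makes that the less natural reading, and one sentence would settle it.

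Finally, the secondary models need no change to their site term. They already carry a random site effect, which covers the linear models and the percentage excretion outcomes. Preferring fixed effects there would be a matter of taste, with no harm shown.

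**Conclusion.** The point holds in a limited form. The pooled primary model, as written, omits the factor within which children are allocated, while the pooled secondary models include it. The treatment comparison remains valid. The cost is an odds ratio nearer 1 than the within-site one, a conservative test and lost power, provided sites differ in the share above the cut-off. For a within-site odds ratio of 0.50 this means about 0.52-0.53 and 1 power point at a logit-scale ICC of 0.1, and 0.56-0.64 and 6-14 points at 0.3-0.5. The larger ICCs, the odds ratio and the shares above the cut-off are assumptions. With no between-site spread there is no cost.

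The LR procedure's collection of all urine up to 5 hours does not fit the two 3-hour sites in Table 2, although the same paragraph allows the choice of window. These passages need to be reconciled.

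**What to change.** - Name site (six levels) in the pooled primary LR model, either as a fixed effect or as the random effect already planned for the secondary outcomes. Because the window is constant within a site, this also absorbs a difference in level between 3-hour and 5-hour sites.
- If the cut-off analysis is kept, say whether the cut-off depends on the window, and do not apply one value to both unless it is justified for both. A site term cannot repair a cut-off that is unsuitable for one window.
- Add a sensitivity analysis of the pooled primary result by collection window.
- Reconcile the collection period in the LR procedure with Table 2.

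The cost is at most five degrees of freedom (six site levels less one) and a few sentences, with no new data. The wording should be settled before the pooled analysis is run.
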